Unfortunately, no research data is available on the beneficial effects of a multidisciplinary approach to proactive palliative care for patients with COPD in terms of reducing the healthcare utilization (for example, hospital readmission) or improving quality of life. However, in a study in male patients predominantly diagnosed with cancer but also with cardiovascular and pulmonary diseases, the benefits of palliative care provision appeared effective compared with usual care [33]. Patients receiving palliative care were less likely to be admitted to the ICU during hospitalization, had lower inpatient cost per day and received better medical care provision compared to usual care patients. Hence proactive palliative care may avoid admission to the ICU for patients with COPD and may help to reduce health care costs. More research data is available concerning the beneficial effects of an early introduction of palliative care for patients with cancer. In a recent study [34] the effect of introducing early palliative care among patients diagnosed with metastatic non-small-cell lung cancer was examined in a randomized controlled trial (RCT). As compared to patients receiving standard care, patients receiving early palliative care had a better quality of life, less depressive symptoms, less aggressive care at the end of life and longer survival.

In the present study the effects of proactive palliative care performed by a specialized palliative care team for patients with COPD on the wellbeing of these patients and their informal caregivers will be examined. We hypothesize that proactive palliative care for patients with COPD will: increase the quality of life of these patients, decrease the number and length of acute hospital admissions and ICU admissions, prolong survival of these patients, decrease the number of patients that die in the ICU, and decrease the level of overburdening of their informal caregivers.

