#### Outcome measures intervention study

1. The primary outcome measure is:

a. Change in quality of life (St George Respiratory Questionnaire (SGRQ) [36]) of the patient 3 months after inclusion

2. The secondary outcome measures are:

Patient-related

a. Change in quality of life (SGRQ) of the patient 6, 9 and 12 months after inclusion

b. Change in quality of life at the end of life (McGill Quality of Life questionnaire (McGill QOL) [37]) 3, 6, 9 and 12 months after inclusion

c. Change in psychological wellbeing (Hospital Anxiety and Depression Scale (HADS) [38]) 3, 6, 9 and 12 months after inclusion

d. Change in illness understanding 3, 6, 9 and 12 months after inclusion

e. Number and length of unexpected hospital admissions

f. Number and length of unexpected ICU admissions

g. Are the choices of Advance Care Planning (ACP) documented in the medical file? (when yes/when no)

h. Place of death (ICU/hospital/hospice/nursing home/at home)

i. Is preferred place of death known? (when yes/when no)

j. Has this wish come true? (when yes/when no)

k. Length of survival of COPD patients with proactive palliative care integrated with standard care versus standard care only

Informal caregiver-related

a. Change in informal caregiver burden (Self-Perceived Pressure from Informal Care questionnaire (SPPIC) [39]) 3, 6, 9 and 12 months after inclusion

b. Change in psychological wellbeing (HADS) at 3, 6, 9 and 12 months after inclusion

c. Change in illness understanding at 3, 6, 9 and 12 months after inclusion

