#### Post-test assessment

A post-test assessment will be performed in all participating hospitals. The medical files of all participating patients will be examined retrospectively regarding the assessment period on the following measures:

● Number and length of hospitalization of unexpected hospital admissions for AECOPD

● Number and length of hospitalization of unexpected ICU admissions for AECOPD

● Are the choices of Advance Care Planning (ACP) documented in the medical file? (when yes/when no)

● Place of death (ICU/hospital/hospice/nursing/home/at home)

● Is preferred place of death known? (when yes/when no)

● Has this wish come true? (when yes/when no)

● Length of survival after meeting conditions for proactive palliative care

● The primary and secondary measures of the indicator study

In order to take account of possible confounding variables, other parameters are: age, gender, marital status, type of admission, (acute or planned), condition of living (single, or living together), place of living (home, residential home, or nursing home), Gold stage, comorbidities, and date of diagnosis.

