**Medical files**						
Number of hospitalisations of unexpected hospital admissions for AECOPD						X
Number of days of unexpected hospital admissions for AECOPD						X
Number of hospitalisations of unexpected ICU admissions for AECOPD						X
Number of days of unexpected ICU admissions for AECOPD						X
Are the choices of ACP documented in the medical file at baseline? (when yes/when no)						X
Are the choices of ACP documented in the medical file after one year or at time of death? (when yes/when no)						X
Did the patient die within one year after inclusion? (when yes/when no)						X
Date of death						X
Place of death (ICU/hospital/hospice/nursing home/at home)						X
Is preferred place of death known? (when yes/when no)						X
Has this wish come true? (when yes/when no)						X
Primary cause of death (pulmonary insufficiency/other cause)						X
Secondary cause of death (pulmonary insufficiency/other cause)						X
Did the patient have an unexpected hospital readmission for AECOPD within 8 weeks? (when yes/when no)						X
Date of first unexpected hospital readmission for AECOPD.						X

B = baseline; m = month; R = retrospectively.

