#### Study parameter(s) intervention study

Frequencies, means and standard deviations will be used to describe the study variables. Differences between the study groups in baseline characteristics and clinical outcomes will be assessed and tested for statistical significance with the use of two-sided Fisher’s exact tests and chi-square tests for categorical variables and independent-samples t-tests for continuous variables. The primary study outcome measure of the intervention study is the change in the score on the SGRQ from baseline to 3 months: a paired *t*-test will be used to test the difference between the groups for statistical significance. Linear mixed models, with adjustment for baseline scores, will be used to study the effect of proactive palliative care on SGRQ outcomes during the follow-up period. The analysis follows the principle of intention to treat. Survival time will be calculated from the date of enrollment to the date of death with the use of the Kaplan-Meier method. A Cox proportional-hazard model will be used to assess the effect of proactive palliative care on survival, with adjustment for demographic characteristics.

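### The ICU-death hypothesis counts patients, but the only matching outcome is place of death, which as listed can be scored only for those who died; the tested outcome should be ICU death yes/no among all qualifying patients

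*Protocol article*

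**What the plan says.** In the Background section on the organization of palliative care, one sentence lists the hypotheses for the intervention. Two stand next to each other: "prolong survival of these patients, decrease the number of patients that die in the ICU". The second is a statement about a number of patients.

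Under *Outcome measures intervention study*, the only outcome that carries the ICU-death hypothesis is item 2h: "Place of death (ICU/hospital/hospice/nursing home/at home". Item 2f counts unexpected ICU admissions and their length, not deaths. The same list of places returns under *Post-test assessment* and in Table 2. None of the three places has a level for a patient who is alive at one year.

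For the analysis, *Study parameter(s) intervention study* gives a general rule, "exact tests and chi-square tests for categorical variables" (Fisher's, two-sided), and says that the analysis follows intention to treat. It names no denominator for place of death.

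The data planned are wider than item 2h alone. *Post-test assessment* says: "The medical files of all participating patients will be examined retrospectively regarding the assessment period on the following measures". Table 2 also lists "Did the patient die within one year after inclusion? (when yes/when no", the date of death and the place of death.

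**The concern.** The hypothesis can be scored for every patient: died in the ICU, yes or no. The listed outcome, on its own, can be scored only for patients who died. Applying the general test for categorical variables to the five listed places leaves survivors nowhere to go, and the comparison becomes one of decedents with decedents.

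That matters here because the article itself expects the intervention to change who dies, and it makes length of survival a separate secondary outcome (2k). A comparison restricted to decedents then conditions on something that the intervention may affect. The ICU share of deaths is a different quantity from the number of patients who die in the ICU, and the two need not move together. With the denominator left open, the choice between them could also be made after the data are seen.

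**Working it through.** **No figure to reproduce.** The article gives no one-year mortality, no ICU share of deaths and no calculation for this outcome. The one figure taken from it is 86 patients per arm (*Sample size calculation*), used as the denominator. All counts of deaths below are assumptions.

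**Relation between the two measures.** In each arm:

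risk of ICU death among all patients = risk of death × ICU share of deaths.

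Let *r* be the ratio (intervention to control) of the risk of death, and *s* the ratio of the ICU share of deaths. The ratio of ICU-death risk among all patients is then *r* × *s*. A decedents-only comparison sees *s*; the hypothesis is about *r* × *s*.

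**When they disagree in direction.** If *r* < 1, then *s* > 1 with *r* × *s* < 1 requires *s* between 1 and 1/*r*:

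- *r* = 0.8: *s* between 1 and 1/0.8 = 1.25
- *r* = 0.67: *s* between 1 and 1/0.67 = 1.49
- *r* = 0.6: *s* between 1 and 1/0.6 = 1.67
- *r* = 1: the interval is empty, so there is no disagreement

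**Worked counts (assumed), 86 per arm:**

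| Case | Control: deaths, in ICU | Intervention: deaths, in ICU | ICU deaths / all patients | ICU deaths / decedents |
|---|---|---|---|---|
| Fewer deaths with intervention | 30, 6 | 20, 5 | 6/86 = 7.0% vs 5/86 = 5.8% | 6/30 = 20% vs 5/20 = 25% |
| Equal deaths | 30, 6 | 30, 4 | 6/86 = 7.0% vs 4/86 = 4.7% | 6/30 = 20% vs 4/30 = 13.3% |
| More deaths with intervention | 20, 5 | 30, 6 | 5/86 = 5.8% vs 6/86 = 7.0% | 5/20 = 25% vs 6/30 = 20% |

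In the first case *r* = 20/30 = 0.67 and *s* = 25/20 = 1.25, which lies inside the interval; *r* × *s* = 5/6 = 0.83. Fewer patients die in the ICU, yet the share among decedents looks worse. The third case is the mirror image. In the second case both measures point the same way.

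**Precision.** Fisher's exact test gives p = 1.00 (all patients) and p = 0.74 (decedents) in the first case, and p = 0.75 and p = 0.73 in the second. Counts of this size would settle nothing on either scale. The table shows how direction can differ, not a likely result.

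**Patients without a level on item 2h.** In the first case (86 − 30) + (86 − 20) = 122 of 172 patients, or 71%, are alive and have no level. More generally, survivors are the majority at any one-year mortality below 50%.

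**The case against.** The strongest reply is that the article never restricts the comparison to decedents. Item 2h is one line naming a variable and its levels, the analysis section gives a general rule and invokes intention to treat, and vital status and place of death are to be taken from the files of all participating patients. The number of ICU deaths per arm over all patients can therefore be obtained. A denominator for one secondary variable is also the sort of detail that an article may leave to a full protocol or analysis plan. Survival is analysed separately by Kaplan-Meier and Cox methods, so a mortality difference would be visible beside place of death. Finally, place of death among those who died is a legitimate descriptive question, and reversal needs both a mortality difference and an ICU share that moves within a limited range.

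Most of this stands. A reader might infer that the protocol confines the test to decedents, that the ICU-death hypothesis goes untested, or that the result will point the wrong way. The documents support none of these: no denominator is stated, the needed data are planned, and no mortality figures are given.

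What remains is that the outcome, as listed in three places, has no level for survivors and does not by itself measure what the hypothesis says will fall. That the data would permit the matching analysis shows that the repair is easy; it does not show that the text specifies it.

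**Conclusion.** The point holds in a limited form. The hypothesis is about the number of patients dying in the ICU; the listed outcome can be scored only for decedents; and the denominator of the comparison is not stated. Since the article expects longer survival, a decedents-only comparison would be selected on a post-treatment event and could mislead, or point the other way, if mortality differs between conditions. Disagreement in direction arises only when the ICU share of deaths changes against mortality by a factor between 1 and 1/*r*, for example up to 1.25 at *r* = 0.8. With equal mortality the two measures agree.

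No size can be attached to this from the documents, and the percentages above rest on assumed counts. It concerns one of eleven patient-related secondary outcomes (2a to 2k) and does not touch the primary analysis, the sample size or data collection. Scoring ICU death over all qualifying patients is nonetheless the better definition: it matches the stated hypothesis, fits intention to treat and avoids selection on survival.

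**What to change.** State that the ICU-death hypothesis is tested as death in the ICU within one year of inclusion (yes/no) among all qualifying patients in both conditions, that is, those who meet two or more indicators. Survivors and patients who die elsewhere are scored 'no'. The variable is derived from death within one year, date of death and place of death, all already in Table 2. Place of death among decedents can still be reported alongside, described as conditional on having died and read next to the survival results.

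The cost is a change of wording, made before outcome data are seen; no new data are needed. The downside is a low event proportion, so the estimate will have wide confidence limits and should be reported with them. The change removes selection on survival only; it does nothing about the non-random choice of hospitals.

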Therefore, recent studies have focused on the best approach and content of palliative care for patients with COPD. It is suggested to start palliative care early beside curative care [31]. Furthermore, good proactive palliative care should at least consist of: 1) a standardized inventory of current and future care needs and a structured organization of proactive palliative care; 2) advance care planning (ACP), which involves the patient (−family)-clinician communication about end-of-life care and the completion of advanced directives [20]. Important components of ACP are discussions about the expected course of the disease and prognosis and counseling concerning preferences for care at the end of life, including spiritual care [19]; 3) development and implementation of a patient-tailored proactive palliative care plan. There are several problems from the patient as well as from the clinician perspective when it comes to satisfactory implementation of ACP and a patient-tailored proactive palliative care plan [7]. First, there are clinician and patient related barriers to discuss ACP [32]. Patients for instance avoid ACP discussions out of fear of suboptimal treatment in case of emergencies while clinicians are concerned that early ACP will take away patients’ hope [20]. Discussions about ACP are therefore unlikely to occur and when they do occur they are likely to be of poor quality [19]. Second, not all clinicians have a special interest in or are qualified to perform proactive palliative care. Finally, delivering proactive palliative care beside curative care for patients with COPD may increase the workload and clinicians may be faced with shortage of time [7]. In order to overcome these problems it is suggested that a multidisciplinary approach to proactive palliative care with better access to specialist palliative care services will help patients with COPD navigate through the continuum of chronic disease management and will improve quality of end-of-life care [7,10].

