### Intervention

In the hospitals in the intervention condition, members of the specialized palliative care teams will receive a special training in the provision of proactive palliative care for patients with COPD. The training will be provided by academic palliative care professionals of the Radboudumc in Nijmegen. These trainings consist of two consecutive meetings of three hours each. The first meeting will take place in the month before start of the assessment. The second meeting will take place in the first month of the assessment. The following topics will be discussed:

● How to communicate end of life aspects with patient and family;

● How to create a patient-tailored proactive palliative care plan;

● How to anticipate on illness- and dying scenarios proactively;

● How to organize transfer of care to lung specialist and general practitioner (GP);

● How to perform a proactive palliative care plan in cooperation with the lung specialist.

During the controlled trial patients in the intervention condition who are assigned for proactive palliative care will meet with a member of the specialized palliative care team within one week after enrollment and at least monthly thereafter in the outpatients setting for at least one year or until death. The main informal caregiver of the patient will be asked to be present at those meetings. Guidelines for the proactive palliative care meetings in the ambulatory setting are adapted from the general guidelines palliative care in the Netherlands [35].

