#### Controlled trial (assessment)

##### Patient

Patients in the control condition will receive standard care (usual care) only. Patients in the intervention condition will receive standard care and, only if they meet two or more criteria of the set of indicators for proactive palliative care they will receive proactive palliative care integrated with standard care. The procedure in the control condition will be first described before describing the procedure in the intervention condition.

In the hospitals in the control condition eligible patients will be recruited the second day after hospital admission. The treating lung specialist will give each eligible patient oral and written information about the study. The written information consists of an information leaflet and two informed consent forms: one for the patient and one for the informal caregiver. In the information leaflet a description of the study, including the nature of participation and phone numbers for study contacts, are given for the patient and the informal caregiver. The lung specialist will obtain written informed consent from the patient prior to enrollment. If a patient has consented, a lung nurse will distribute questionnaires for completion on the sixth day of hospital stay or in case the patient is discharged earlier on the day before leaving the clinic. After hospital discharge the patient will be asked by the study coordinator to complete questionnaires every 3 month until the end of the study or until death. The questionnaires will be sent to the patient by mail. A stamped retour envelope will be enclosed.

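### Whether the preferred place of death was achieved can be scored only where the preference is known, which the intervention is meant to change, so a between-arm test of it is open to bias of unknown size and direction

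*Protocol article*

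**What the plan says.** The Protocol article, under Outcome measures intervention study, lists three linked patient-related secondary outcomes: place of death (item h), then "Is preferred place of death known? (when yes/when no" (item i), then "Has this wish come true? (when yes/when no" (item j). The Post-test assessment section and Table 2 repeat items i and j as data taken from patient records: "The medical files of all participating patients will be examined retrospectively regarding the assessment period".

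The arms differ in exactly the activity that makes a preference known. The Intervention section lists among the training topics for the palliative care teams "How to communicate end of life aspects with patient and family", together with patient-tailored care plans, and contacts follow at least monthly. The background section on organization of care counts advance care planning as a core element, including "counseling concerning preferences for care at the end of life, including spiritual care". For the other arm, the Patient section says: "Patients in the control condition will receive standard care (usual care) only".

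On analysis, the section Study parameter(s) intervention study says: "Differences between the study groups in baseline characteristics and clinical outcomes will be assessed and tested for statistical significance". Fisher's exact and chi-square tests are named for categorical variables. The other methods in that section concern the SGRQ and survival, so this sentence is the only one that covers item j.

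**The concern.** In item j, the wish referred to is the preference of item i. A death without a known preference has no value for item j and drops out of a comparison of proportions. Item i is measured after baseline, is listed as an outcome and is a target of the intervention. A test of item j between arms therefore conditions on something the intervention may change.

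If those whose preference reaches the file under usual care differ from those whose preference is recorded after systematic discussion, the two proportions describe different kinds of death. A difference could then appear with no effect on where people die relative to their wishes, or a real effect could be hidden. The analysis by intention to treat does not help, because it cannot supply a value where no preference is on file.

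**Working it through.** **No plan figure to reproduce.** The article gives no mortality, no share of known preferences, no fulfilment rate and no power for this outcome. The mechanism is therefore checked with assumed inputs.

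**Assumptions.** Half of deaths are anticipated, with the wish met in 70%. Half are sudden, with the wish met in 30%. This is the same in both arms, so the true rate is 0.5 × 0.70 + 0.5 × 0.30 = 50% in each and there is no effect. Only the chance that the preference is known varies.

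**Formula.** Met among known = Σ(share × known × met) / Σ(share × known).

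Row A, control: (0.5 × 0.30 × 0.70 + 0.5 × 0.10 × 0.30) / (0.5 × 0.30 + 0.5 × 0.10) = 0.120 / 0.20 = 60.0%.

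Row A, intervention: (0.5 × 0.80 × 0.70 + 0.5 × 0.70 × 0.30) / (0.5 × 0.80 + 0.5 × 0.70) = 0.385 / 0.75 = 51.3%.

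| Row | Known, control (anticipated/sudden) | Known, intervention | Met among known, control | Met among known, intervention | Difference, points |
|---|---|---|---|---|---|
| A | 30% / 10% | 80% / 70% | 60.0% | 51.3% | -8.7 |
| B | 40% / 10% | 80% / 60% | 62.0% | 52.9% | -9.1 |
| C | 20% / 5% | 90% / 80% | 62.0% | 51.2% | -10.8 |
| D | 30% / 30% | 80% / 80% | 50.0% | 50.0% | 0 |
| E | 30% / 10% | 30% / 10% | 60.0% | 60.0% | 0 |
| F (A with the two types swapped) | 10% / 30% | 70% / 80% | 40.0% | 48.7% | +8.7 |

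Row F: control (0.035 + 0.045) / 0.20 = 40.0%; intervention (0.245 + 0.120) / 0.75 = 48.7%.

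In these rows a spurious difference appears only when recording differs between arms and is also related to the chance that the wish is met (rows D and E show zero). Its sign follows that relation (A against F).

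**All deaths as denominator.** In row A, preference documented and achieved gives 12% in control and 38.5% in intervention, a gap of 26.5 points with no effect on achievement; it comes from documentation alone. Counting the unknown preferences as all unmet and then as all met gives bounds of 12% to 12 + 80 = 92% in control and 38.5% to 38.5 + 25 = 63.5% in intervention. Both ranges contain the true 50%.

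**Numbers available.** The sample size section asks for 86 patients per arm. With an assumed one-year mortality of 20% to 40%, that is about 17 to 34 deaths per arm. With 20% known in control and 75% in intervention (row A), item j would rest on about 3 to 7 control deaths and 13 to 26 intervention deaths.

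**The case against.** The article never names item j in its statistical section and sets no denominator for it. Detail of that kind is often left to an analysis plan, which is not shown here. Items h, i and j are listed separately, so a reader of the results would see how many preferences were known. The concern also rests on assumed rates.

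Much of this stands. The restriction to known preferences is implied by the wording of item j, not stated as an analysis set, and an unseen plan could deal with it. What remains is that the outcome as worded is conditional and that the one applicable analysis sentence calls for a test between groups. Showing item i beside item j makes the selection visible but does not make the test interpretable.

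A reader might go further and infer that the comparison is biased against the intervention, so that an intervention getting more people to their preferred place would look worse. Assume, for example, that preferences are known in 30% of control and 70% of intervention deaths, and met in 70% and 60% of those. Then item j reads 70% against 60%, while documented and achieved over all deaths reads 0.30 × 0.70 = 21% against 0.70 × 0.60 = 42%. That apparent reversal counts every unknown preference as a failure. If a share x of unknown wishes was met in both arms, total achievement is 0.21 + 0.70x in control and 0.42 + 0.30x in intervention. The two are equal at x = 0.21 / 0.40 = 0.525, and above that control is ahead. The document does not give x, so it does not support the stronger reading.

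**Conclusion.** The point holds in a limited form. A between-arm test of item j conditions on item i, which the intervention is meant to change, and nothing else in the article repairs this. The test is open to bias, but the article shows neither that bias will occur nor which way it would go. It arises if the intervention changes how often the preference is known, which is its evident aim but not a figure in the document, and if being known is related to the chance that the wish is met. Under the assumed inputs the spurious difference runs from -10.8 to +8.7 points, with zero also possible.

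Replacing item j by the all-deaths composite as the tested measure of achievement is not supported either, since under the same inputs it shows 26.5 points with no true effect on achievement.

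The importance is small: one secondary outcome, in a design that is not randomized, resting on few control deaths under any of the assumed rates. The primary outcome and the sample size are not affected.

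One limit remains after any change to item j. Items i and j both look at deaths, and the protocol also expects the intervention to "prolong survival of these patients, decrease the number of patients that die in the ICU", so who dies within the year may itself differ between arms.

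**What to change.** - Compare item i (preference known, yes or no) over all deceased qualifying patients in each arm, and note that the restriction to deaths is itself a selection.
- Report item j descriptively only. Give, per arm, the number of deaths, the number with a known preference and the number of those in whom it was met. Make no between-arm test and draw no conclusion about effect.
- Optionally show preference documented and achieved among all deaths beside these. Label it as a composite that also reflects documentation, and give bounds that count unknown preferences as all met and as all unmet. It should not be read as the effect on achieving the preferred place of death.

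The cost is a few sentences in the outcome and analysis sections. Table 2 already collects date and place of death, whether the preference was known and whether it was fulfilled, so no new data are needed. What is given up is one significance test that could not have been interpreted.
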